## Abstract

New therapies are needed to prevent exacerbations, improve quality of life and slow disease progression in bronchiectasis. Inhibition of cathepsin C (CatC) activity has the potential to decrease activation of neutrophil-derived serine proteases in patients with bronchiectasis, thereby reducing airway inflammation, improving symptoms, reducing exacerbations and preventing further airway damage. Here we present the design of a phase 2 trial (Airleaf™; NCT05238675) assessing the efficacy and safety of a novel CatC inhibitor, BI 1291583, in adult patients with bronchiectasis. This multinational, randomised, double-blind, placebo-controlled, parallel-group, dose-finding study has a screening period of at least 6 weeks, a treatment period of 24–48 weeks and a follow-up period of 4 weeks. ∼240 adults with bronchiectasis of multiple aetiologies will be randomised to placebo once daily, or BI 1291583 1 mg once daily, 2.5 mg once daily or 5 mg once daily in a 2:1:1:2 ratio, stratified by *Pseudomonas aeruginosa* infection and maintenance use of macrolides. The primary efficacy objective is to evaluate the dose–response relationship for the three oral doses of BI 1291583 *versus* placebo on time to first pulmonary exacerbation up to Week 48 (the primary end-point). Efficacy will be assessed using exacerbations, patient-reported outcomes, measures of symptoms, sputum neutrophil elastase activity and pulmonary function testing. Safety assessment will include adverse event reporting, physical examination, monitoring of vital signs, safety laboratory parameters, 12-lead electrocardiogram, and periodontal and dermatological assessments. If efficacy and safety are demonstrated, results will support further investigation of BI 1291583 in phase 3 trials.

## Introduction

Bronchiectasis is a heterogeneous respiratory syndrome characterised by chronic airway inflammation; abnormal, scarred and irreversibly dilated bronchi; mucus plugging and subsequent airflow obstruction, facilitating bacterial infection [1–4]. The pathogenesis of bronchiectasis is not fully understood; however, once established, patients show evidence of chronic inflammation, infection, impaired mucociliary clearance and progressive structural lung damage. The complex interaction between these features (the so-called “vicious vortex”) leads to exacerbations and decline in pulmonary function, with associated morbidity and mortality [5].

Bronchiectasis has been described as an emerging global epidemic [6], with prevalence and incidence rates increasing worldwide [7, 8]. Prevalence increases with age and female sex [8, 9], and there is geographical heterogeneity in underlying disease aetiology [10], which ranges from well-characterised genetic diseases such as cystic fibrosis and primary ciliary dyskinesia, to a range of autoimmune diseases (for example, inflammatory bowel disease or rheumatoid arthritis), hypersensitivity disorders such as allergic bronchopulmonary aspergillosis, immunodeficiencies, and chronic airway inflammatory diseases such as COPD and asthma [5]. Each underlying aetiology considered individually may be rare but taken together bronchiectasis occurs in up to 566 people per 100  000 (0.6%) [11], with the UK reporting the highest global prevalence and incidence (566.1 per 100 000 women and 485.5 per 100 000 men, and 35.2 per 100 000 person-years in women and 26.9 per 100 000 person-years in men, respectively [7]). In addition to significant morbidity and mortality, bronchiectasis imposes a significant disease burden on patients due to reduced quality of life [12]. The disease also has a significant economic impact, including increased healthcare utilisation and costs, and loss of productivity [13].

Neutrophils are abundant in the airways of patients with bronchiectasis, neutrophilic inflammation is a central feature of the disease (figure 1), and the extent of this inflammation is associated with disease severity and progression [14, 15]. While neutrophilic inflammation is closely linked to infection, inflammation can also progress in the absence of infection. In many cases of the disease, antibiotic treatment is insufficient to control infection [16].

**FIGURE 1 F1:**
[figure not shown]
The “vicious vortex” in bronchiectasis, the key role of neutrophilic inflammation and the expected effects of inhibiting cathepsin C during myelopoiesis. A1AT: α-1 antitrypsin; CatC: cathepsin C; CatG: cathepsin G; ECM: extracellular matrix; IL-1β: interleukin-1β; IL-8: interleukin-8; MMP: matrix metallopeptidase; NE: neutrophil elastase; NSP: neutrophil-derived serine protease; PR3: proteinase 3; SLPI: secretory leukocyte peptidase inhibitor; TNF-α: tumour necrosis factor-α.

Release of inflammatory effectors from neutrophils contributes to the inflammatory environment [17]. An imbalance between neutrophil-derived serine proteases (NSPs) (neutrophil elastase (NE), proteinase 3 (PR3) and cathepsin G (CatG)) and their inhibitors has been implicated in many chronic inflammatory respiratory diseases [18–21], including bronchiectasis [7]. Sputum NE activity was shown to be associated with increased risk and frequency of exacerbations, infections, hospitalisations and mortality [22, 23]. Levels of PR3 were found to be raised in patients with bronchiectasis during exacerbations compared with stable disease, correlating with levels of NE [24]. CatG activity was also found to cause dysfunction of ciliated cells and destruction of airway epithelium in patients with bronchiectasis, and activity correlated with disease severity [25].

NE, PR3 and CatG are activated by cathepsin C (CatC) (also known as dipeptidyl peptidase 1) during myelopoiesis in the bone marrow [26]. Inhibition of CatC is therefore expected to result in decreased levels of active NE, CatG and PR3 in neutrophils recruited to the lungs of patients with bronchiectasis. Since high, uncontrolled NSP levels have been shown to impair defence against bacterial infection, impair mucociliary clearance, promote mucus hypersecretion, and degrade elastin and other extracellular matrix components [7], effective blockade of NSPs could ameliorate each component of the vicious vortex. Interrupting the vicious vortex, possibly at multiple locations, through CatC inhibition, will likely reduce inflammation, lung destruction, mucus production and infection, and have secondary anti-inflammatory effects (figure 1).

No drug is licensed for the treatment of bronchiectasis. Therefore, there is a high unmet need for a novel bronchiectasis treatment that reduces aberrant inflammation, addresses exacerbations, and improves symptoms and patient quality of life.

BI 1291583 is a novel CatC inhibitor under investigation as a potential disease-modifying therapy for patients with bronchiectasis. *In vitro* and *in vivo* preclinical analyses demonstrated that BI 1291583 is a reversible, highly potent and highly selective inhibitor of CatC, with downstream dose-dependent effects on the production of active NE and PR3 after lipopolysaccharide challenge, and a high bone marrow-to-plasma distribution ratio. Five phase 1 trials in healthy volunteers, with dosing regimens of BI 1291583 based on effective dose calculations from the above preclinical analyses, demonstrated a good safety and tolerability profile up to 40 mg single doses and up to 10 mg multiple doses [27]. Taking the drug with food did not affect systemic exposure, and there was a low (up to twofold) increase in exposure with coadministration with itraconazole (a strong cytochrome and P-glycoprotein inhibitor) [27]. Adverse events of special interest (AESIs) related to skin, reported in previous trials of other CatC inhibitors in bronchiectasis [28–30], were observed more frequently in treated participants overall; however, cases were mild and those related to study drug were low (single cases except in the 5 mg dose), and were reported in both placebo and treated groups with the same frequency [27].

Based on the promising preclinical and phase 1 results, a multinational, randomised, double-blind, placebo-controlled, parallel-group, dose-finding phase 2 study in adult patients with bronchiectasis is now underway. Here we present and discuss the trial methodology.

## Research methods

### Study design

This phase 2 study (Airleaf™; NCT05238675) is a multinational, randomised, double-blind, placebo-controlled, parallel-group, dose-finding study that will be conducted in ∼23 countries. The study will comprise a screening period of at least 6 weeks, a treatment period of at least 24 weeks and up to 48 weeks, and a follow-up period of 4 weeks (figure 2).

**FIGURE 2 F2:**
[figure not shown]
Study design. A1AT: α-1 antitrypsin; ABPA: allergic bronchopulmonary aspergillosis; CF: cystic fibrosis; EOS: end of study; FEV_1_: forced expiratory volume in 1 s; NE: neutrophil elastase; QOL-B: Quality of Life Questionnaire-Bronchiectasis; SGRQ: St George's Respiratory Questionnaire.

Approximately 240 adults with bronchiectasis will be randomised in a 2:1:1:2 ratio, respectively, to placebo once daily (n=80), BI 1291583 1 mg once daily (n=40), BI 1291583 2.5 mg once daily (n=40) or BI 1291583 5 mg once daily (n=80). The randomisation will be stratified by *Pseudomonas aeruginosa* infection (yes/no) and by macrolide antibiotic maintenance (yes/no). Maintenance therapy with oral or inhaled antibiotics will be allowed if the patient is on stable treatment >3 months prior to randomisation and if an exacerbation occurred in the past year while being on that therapy. Maintenance therapy with bronchodilators will also be permitted during the treatment period, except 6–24 h prior to pulmonary function tests. A list of the baseline clinical data to be collected can be found in the supplementary material.

Once randomised, patients will be treated for at least 24 weeks and up to 48 weeks. At the planned end of treatment date of the last patient randomised (24 weeks), end of treatment will apply to all ongoing patients, and they will conclude study participation (end of study). Patients who prematurely and permanently discontinue study medication will be asked to attend future visits as scheduled.

### Objectives and end-points

The primary efficacy objective is to evaluate the dose–response relationship for oral 1 mg, 2.5 mg or 5 mg once daily BI 1291583 *versus* placebo on time to first pulmonary exacerbation up to Week 48 after first drug administration (primary end-point). Secondary objectives are to test the superiority of BI 1291583 5 mg *versus* placebo on the primary end-point and on the key secondary end-point (rate of pulmonary exacerbations up to Week 48), performed in a hierarchical order. Additional secondary efficacy end-points, along with safety, further clinical and pharmacokinetic end-points are described in table 1.

**TABLE 1 TB1:** Additional secondary efficacy, and safety, further clinical and pharmacokinetic end-points

**Secondary efficacy**	**Safety**	**Further clinical** ** ^#^ **	**Pharmacokinetic**
Absolute change from baseline in QOL-B domain scores at Week 24 after first drug administration	Percentage of patients with treatment-emergent AEs up to the end of the REP (Week 52)	Change from baseline in cough frequency	C_pre,N_ C_pre,ss_
Relative change from baseline in NE activity in sputum at Week 12 after first drug administration	Physical examination, vital signs, safety laboratory parameters, 12-lead ECG	Change from baseline in PRO total and domain scores, and VAS scores for cough severity, cough urgency and shortness of breath	
Absolute change from baseline in SGRQ symptoms score at Week 24 after first drug administration		Number of subjects hospitalised due to pulmonary exacerbations	
Absolute change from baseline in FEV_1_ % predicted at Week 24 after first drug administration	Periodontal and dermatological assessments		
Occurrence of an exacerbation by Week 24 after first drug administration			

QOL-B: Quality of Life Questionnaire-Bronchiectasis; AE: adverse event; REP: residual effects period; C_pre,N_: pre-dose BI 1291583 plasma concentration immediately before administration of the Nth dose after N−1 doses were administered; C_pre,ss_: pre-dose BI 1291583 plasma concentration immediately before administration at pharmacokinetic steady state; NE: neutrophil elastase; ECG: electrocardiogram; PRO: patient-reported outcome; VAS: visual analogue scale; SGRQ: St. George's Respiratory Questionnaire; FEV_1_: forced expiratory volume in 1 s. **^#^**: at Week 24.

Additional objectives of the trial are to confirm BI 1291583-mediated reduction of NE activity in sputum at Week 12, assess lung function and quality of life after 24 weeks of treatment, assess additional exploratory measures of efficacy (including exacerbations, lung function and patient-reported outcomes), and evaluate pharmacokinetics, changes over time in blood and sputum biomarkers, safety and tolerability.

### Outcome assessments

Efficacy will be assessed using measures of disease worsening (time to first, and rate of, pulmonary exacerbation), patient-reported outcomes (*e.g.* Quality of Life Bronchiectasis Questionnaire, St. George's Respiratory Questionnaire (SGRQ) symptoms score and visual analogue scales), relative change from baseline in sputum NE activity and pulmonary function (forced expiratory volume in 1 s (FEV_1_) % predicted).

Safety will be monitored throughout the study by assessment of adverse events, physical examination, monitoring of vital signs, safety laboratory parameters and 12-lead electrocardiogram. As in the phase 1 trials of BI 1291583 [27], and given the safety profile observed with other CatC inhibitors [28, 30], assessment of safety will include the occurrence of hyperkeratosis and periodontal disease as AESIs. A list of potential adverse events based on phase 1 trials of BI 1291583 can be found in the supplementary material.

Pharmacokinetic analysis of BI 1291583 will be performed using blood samples.

### Key inclusion and exclusion criteria

This trial will enrol patients with a computed tomography-confirmed diagnosis of bronchiectasis and a history of pulmonary exacerbations requiring antibiotic treatment. Patients with idiopathic bronchiectasis, as well as those with a broad range of underlying aetiologies, including, but not limited to, COPD, asthma, post-infectious rheumatoid arthritis or primary ciliary dyskinesia, will be eligible for this trial. In the 12 months before Visit 1, patients must have had either at least two exacerbations, or one exacerbation and be symptomatic as indicated by a SGRQ symptoms score of >40. The inclusion of symptoms in addition to exacerbation history is based on the observation that the risk of exacerbation increases by 10% for each 10-point increase in the SGRQ symptoms score as well as the demonstrated association between neutrophilic inflammation and symptoms in bronchiectasis [4, 31, 32]. Patients with cystic fibrosis and those with underlying diseases and/or treatments that represent an increased risk (*e.g.* those with a compromised immune system) are excluded from this trial. Patients with Papillon–Lefèvre syndrome (PLS) (a rare genetic disease with loss-of-function mutations in both alleles of the CatC gene), or hyperkeratosis of any aetiology, are likewise excluded from our trial, as are patients with medical conditions associated with periodontal disease (to be evaluated by a periodontist or dentist). Key inclusion and exclusion criteria are detailed in table 2. The full list is available in the supplementary material.

**TABLE 2 TB2:** Key inclusion and exclusion criteria

**Inclusion criteria**	**Exclusion criteria**
Male or female, aged ≥18 years^#^ and ≤85 years at screening	AST and/or ALT >3× ULN at Visit 1
Signed and dated written informed consent prior to admission to the study, in accordance with Good Clinical Practice and local legislation	Estimated glomerular filtration rate according to CKD-EPI formula <30 mL·min^−1^ at Visit 1
Women of childbearing potential^¶^ adhering to contraception requirements	Absolute blood neutrophil count <1000/mm^3^ at Visit 1
Clinical history consistent with bronchiectasis (cough, chronic sputum production and/or recurrent respiratory infections) and investigator-confirmed diagnosis of bronchiectasis by CT scan	Acute SARS-CoV-2 infection
History of pulmonary exacerbations requiring antibiotic treatment. In the 12 months before Visit 1, patients must have had either: 1) at least two exacerbations, or 2) one exacerbation and an SGRQ symptoms score of >40 at Screening Visit 1	Current smokers, or stopped smoking only within 3 months of screening, or not willing to maintain non-smoking status for the duration of the study
Current sputum producers with a history of chronic expectoration who are able to provide a spontaneous sputum sample at Screening Visit 1	Current diagnosis of cystic fibrosis, hypogammaglobulinaemia, common variable immunodeficiency, α1-antitrypsin deficiency, or allergic bronchopulmonary aspergillosis requiring treatment
	Any acute infections (including respiratory infections)
	Any mycobacterial infections, including pulmonary non-tuberculous mycobacterial disease, currently being treated
	Severe periodontal disease (to be evaluated by a periodontist or dentist) or palmar keratosis
	Any recent change in dose or regimen of maintenance bronchiectasis treatment
	Any medical condition that could interfere with participation or conduct of the study

AST: aspartate aminotransferase; ALT: alanine aminotransferase; ULN: upper limit of normal; CKD-EPI: Chronic Kidney Disease Epidemiology Collaboration; CT: computed tomography; SARS-CoV-2: severe acute respiratory syndrome coronavirus 2; SGRQ: St George's Respiratory Questionnaire. ^#^: ≥ 19 years in Republic of Korea; ^¶^: if allowed according to regulatory requirements.

### Recruitment and sample size calculation

With the planned sample size of 240 patients in a 2:1:1:2 allocation ratio, under the assumption of a hazard ratio of 0.5 for BI 1291583 5 mg once daily *versus* placebo, 0.6 for 2.5 mg once daily *versus* placebo and 0.8 for 1 mg once daily *versus* placebo, an overall power of at least 90% is achieved to demonstrate a non-flat dose–response curve in the dose-finding analysis and for the comparison of BI 1291583 5 mg *versus* placebo on the primary end-point. Overall exacerbation rates will be monitored blinded in order to potentially modify sample size and study duration (up to a maximum of 48 weeks), if needed. Such reassessment is important given the potential reduction in exacerbations observed during the COVID-19 pandemic and uncertainty over how long ongoing changes in behaviour will affect exacerbation rates [33].

### Planned analyses and assessments

The primary efficacy analysis consists of a multiple comparison and modelling (MCPMod)-based testing (with respect to a non-flat dose–response curve). MCPMod is used to evaluate several possible dose–response models (patterns), and to identify the best-fitting model or subset of models while keeping full control of the type I error at 0.05, one-sided. For the confirmatory testing of the primary end-point, the equality of the hazard ratios will be tested by the Wald test for the treatment effect in a Cox proportional hazards model at the one-sided 2.5% significance level. The effect of BI 1291583 5 mg *versus* placebo regarding the rate of pulmonary exacerbations will be analysed using a negative binomial model. In both models, the stratification factors will be included as covariates. Subgroup analyses will be carried out on the primary end-point according to baseline history of pulmonary exacerbations, baseline maintenance use of macrolides and *Pseudomonas aeruginosa* colonisation status. Details on the handling of missing data can be found in the supplementary material.

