A further key strength of our study is the inclusion of patients with a history of only one exacerbation requiring antibiotic treatment and an SGRQ symptoms score of >40. The inclusion of the symptoms score enriches for future exacerbations in any patients emerging from COVID-19 lockdown where a potential reduction in observed exacerbations may occur, as the risk of exacerbation is not predicted just by history of exacerbations but also by symptoms [31]. In addition, the sample size adjustment allowed by our study is especially important because associated social isolation features may result in potential future reductions in observed exacerbations [33].

The key differentiating factor in our study is the inclusion of a novel broad patient population with regard to underlying aetiologies in Airleaf™, specifically the inclusion of patients with a primary diagnosis of asthma and COPD. Such patients have generally been excluded from bronchiectasis studies. They are included here as active neutrophilic inflammation is the driver of bronchiectasis in these patients and therefore targetable for medication, and their inclusion allows us to investigate a precision medicine approach targeting patients with bronchiectasis in need of an anti-inflammatory treatment. This recognises that these are patient populations with a high burden of illness and neutrophilic inflammation that may benefit from a CatC inhibitor [40–42]. In addition, bronchiectasis as a primary diagnosis may be missed in patients who smoke and are, therefore, labelled with COPD [40, 41]. In either case, the underlying neutrophilic inflammatory processes may benefit from CatC inhibition.

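### The Cox and negative binomial models name only the two stratification factors as covariates; adding exacerbation history and SGRQ symptoms score would be a modest, nearly free gain in efficiency

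*Protocol article*

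**What the plan says.** All references are to the protocol article.

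- **Planned analyses and assessments**, on the Cox and negative binomial models: "In both models, the stratification factors will be included as covariates". No other covariate is named.
- **Study design** (text below figure 2): randomisation is stratified by *P. aeruginosa* "infection (yes/no) and by macrolide antibiotic maintenance (yes/no").
- **Key inclusion and exclusion criteria**: "the risk of exacerbation increases by 10% for each 10-point increase in the SGRQ symptoms score". Table 2 requires, in the 12 months before Visit 1, "1) at least two exacerbations, or 2) one exacerbation and an SGRQ symptoms score of >40 at Screening Visit 1".
- **Discussion**: "the risk of exacerbation is not predicted just by history of exacerbations but also by symptoms".
- **Planned analyses and assessments** also makes history an analysis variable: "Subgroup analyses will be carried out on the primary end-point according to baseline history of pulmonary exacerbations". The SGRQ symptoms score appears in neither the covariate list nor the subgroup list.
- **Table 1** has change from baseline in SGRQ symptoms score at Week 24 as a secondary end-point, which implies a baseline score for all patients.

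**The concern.** The sponsor identifies two predictors of its primary outcome and recruits on them, but neither stratifies on them nor names them as covariates.

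Leaving out a prognostic variable costs something different in each model. In a Cox model, the hazard ratio from the smaller model is pulled towards 1, which costs some power. In a negative binomial model, the unexplained variation goes into the dispersion and widens the standard error of the log rate ratio.

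Events may be scarce: the article itself expects that exacerbation rates could be low after COVID-19 and keeps a blinded reassessment for that reason. Baseline adjustment is a much cheaper, if small, protection.

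**Working it through.** **1. The stated power.** The sample size section gives an overall power of at least 90% "under the assumption of a hazard ratio of 0.5 for BI 1291583 5 mg once daily" against placebo. The test is a Wald test "in a Cox proportional hazards model at the one-sided 2.5% significance level", with 80 patients per arm.

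- Events for 90% power, Schoenfeld: 4 × (1.960 + 1.282)² / (ln 0.5)² = 4 × 10.51 / 0.4805 = 87.5, so 88.
- Freedman: [(1 + 0.5)/(1 − 0.5)]² × 10.51 = 94.6, so 95.

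The article gives no event rate, so I assume a placebo event probability p, set the 5 mg probability to 1 − (1 − p)^0.5, and use power = Φ(½ √events × 0.693 − 1.960).

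| Assumed p (placebo) | Power, 5 mg v placebo |
|---|---|
| 0.40 | 0.688 |
| 0.50 | 0.788 |
| 0.60 | 0.862 |
| 0.65 | 0.890 |
| 0.70 | 0.914 |
| 0.75 | 0.934 |

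At p = 0.67, events = 80 × (0.67 + 0.426) = 87.6. The stated power for this comparison is therefore attainable if about 67% or more of placebo patients have an event. The article can neither confirm nor refute it.

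**2. Strength of the one quantified predictor.** A 10% rise per 10 points is ln 1.10 = 0.0953 per 10 points. With an assumed SGRQ SD of 20, the SD of the log hazard due to SGRQ is 2 × 0.0953 = 0.19, which is weak. The article gives no effect size for exacerbation history.

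**3. Simulation of the two analyses.** Data: 80 v 80, follow-up uniform over 24 to 48 weeks, the article's eligibility rule, and a hazard ratio of 0.5 conditional on the covariates. Each data set was fitted with treatment + strata, and again with history (1, 2, 3 or more) and SGRQ score added. Taken from the article: the SGRQ effect. Assumed: SGRQ mean 50 and SD 15 to 25, rate ratio 1.0 to 1.8 per history category, placebo rate 1.4 to 2.0 per year, gamma frailty variance 0.5 or about 0. There were 1,500 Cox runs per scenario and up to 150 negative binomial runs.

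Cox model, power:

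| Scenario | Strata only | Both added | Change |
|---|---|---|---|
| SGRQ alone prognostic | – | – | about −1 to +1.4 points |
| History rate ratio 1.5 | 0.763 | 0.777 | +1.4 points |
| History rate ratio 1.8 | 0.736 | 0.774 | +3.8 points |

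An example of how the gain arises: the log hazard ratio moves from −0.575 to −0.600, so it grows by 0.600/0.575 − 1 = 4.3%, while its standard error goes from 0.216 to 0.220, up 1.9%. The gain comes from less attenuation; the standard error does not shrink.

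A second set (2,500 Cox replicates, SGRQ SD 18, 63 to 69% of placebo patients with an event) gave gains of 3.9 points (83.3% to 87.2%) and 3.4 points (86.0% to 89.4%) at a history rate ratio of 1.5, 1.0 to 1.4 points at 1.3, and 0.5 to 1.1 points at 1.15. Under the null, rejection was 2.4% and 2.5%.

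Negative binomial model, standard error of the log rate ratio:

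| Scenario | Strata only | Both added | Fall in SE | Fall in variance |
|---|---|---|---|---|
| SGRQ alone prognostic | 0.195 | 0.194 | 0.5% | 1% |
| History rate ratio 1.5 | 0.202 | 0.195 | 3.5% | 7% |
| History rate ratio 1.8 | 0.204 | 0.189 | 7.4% | 14% |

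Negative binomial power changed by about −1 to +3 points, within simulation noise. Some fits failed to converge, mostly with frailty near zero (99 of 150 usable there).

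**The case against.** The article says that the stratification factors are included; it does not say that nothing else is. It condenses a longer protocol, and further covariates may stand in documents not shown. Adjusting for the stratification factors is sound, and calling a variable a predictor in order to justify eligibility does not oblige the trial to adjust for it. The only prognostic effect that the article quantifies is too weak to matter much, and the larger gains need a history effect that it does not give. The simulation also treats the hazard ratio of 0.5 as conditional on history and symptoms, which the sample size section does not say. Table 2 needs the SGRQ score only for patients with one exacerbation. History is already planned as a subgroup variable.

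Most of this stands and sets the size of the point. The fix must be conditional on what the full documents say, and no error is shown. If 0.5 was meant for the strata-only model, its attenuation is no loss against the plan, though the richer model can still gain power on the same data. Two objections carry less weight: the SGRQ change end-point in table 1 implies a baseline score for everyone, and a subgroup analysis by history does not replace adjustment. Both covariates remain plausible and cheap to add.

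**Conclusion.** A minor missed efficiency. Naming both covariates would be worth roughly 0 to 4 points of Cox power for 5 mg v placebo: about 1 point or less if only the SGRQ effect applies, and more only under an assumed history rate ratio of about 1.5 to 1.8. For the exacerbation rate it would be worth a 0 to 7% smaller standard error. Some scenarios show no gain or a loss of about 1 point.

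A reader might infer more than the document supports:

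- **That precision is lost in the Cox model.** It is not; adjustment raises that standard error by about 1 to 2%.
- **That the trial falls short of its stated power.** The simulated power levels depend on assumed rates and frailty and do not show this.
- **That the test is biased or its type I error inflated.** The strata-only analysis is valid.
- **That chance imbalance in the 40-patient arms would distort the dose-response curve.** Such imbalance is random, the article does not say which estimates feed MCPMod, and no MCPMod analysis was simulated.
- **That other covariates are ruled out.** That is only an inference from a condensed text.

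**What to change.** Unless the full protocol or SAP already does so, prespecify before unblinding two further baseline covariates in the Cox and negative binomial models: number of exacerbations in the 12 months before Visit 1 (1, 2, 3 or more) and baseline SGRQ symptoms score (continuous). Add them also to the model that supplies the MCPMod estimates, if that is a Cox model. Keep the stratification factors. Confirm that a baseline SGRQ score is recorded for every patient. State that the hazard ratio is then conditional on these covariates as well, and report the strata-only model as a sensitivity analysis.

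The cost is a few sentences, a slightly different conditional estimand and one extra sensitivity analysis. No new patients or visits are needed.
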